## Abstract

**Background:**

The aim of the Boost study was to produce a persistent increase in fruit and vegetable consumption among 13-year-olds. This paper describes the development, implementation and evaluation of a school-and community-based, multi-component intervention guided by theory, evidence, and best practice.

**Methods/design:**

We used the Intervention Mapping protocol to guide the development of the intervention. Programme activities combined environmental and educational strategies and focused on increasing access to fruit and vegetables in three settings: School: Daily provision of free fruit and vegetables; a pleasant eating environment; classroom curricular activities; individually computer tailored messages; one-day-workshop for teachers. Families: school meeting; guided child-parent activities; newsletters. Local community: guided visits in grocery stores and local area as part of classroom curriculum; information sheets to sports-and youth clubs.

The Boost study employed a cluster-randomised controlled study design and applied simple two-stage cluster sampling: A random sample of 10 municipalities followed by a random sample of 4 schools within each municipality (N = 40 schools). Schools were randomised into a total of 20 intervention-and 20 control schools. We included all year 7 pupils except those from school classes with special needs. Timeline: Baseline survey: August 2010. Delivery of intervention: September 2010-May 2011. First follow-up survey: May/June 2011. Second follow-up survey: May/June 2012. Primary outcome measures: Daily mean intake of fruit and vegetables and habitual fruit and vegetable intake measured by validated 24-hour recall-and food frequency questionnaires. Secondary outcome measures: determinants of fruit and vegetable intake, positive side-effects and unintended adverse effects. Implementation was monitored by thorough process evaluation.

**Discussion:**

The baseline data file included 2,156 adolescents (95%). There was baseline equivalence between intervention-and control groups for sociodemographics, primary outcomes, and availability at home, school and sports-and youth clubs. Significantly larger proportions of pupils in the control group had parents born in Denmark. The study will provide insights into effective strategies to increase fruit and vegetable intake among teenagers. The study will gain knowledge on implementation processes, intervention effects in population subgroups with low intake, and opportunities for including local communities in interventions.

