#### Proximal outcomes of the intervention: Changes in determinants

Environmental, social and personal determinants were measured by questionnaires to pupils, parents, principals and representatives from sports-and youth clubs. The intervention programme was designed to create significant, positive changes in specific determinants of teenagers' FV consumption at intervention schools at 1^st ^follow-up versus baseline and control schools. As shown in Table 4 the Boost study is characterised by thorough measures of both perceived and actual social and environmental influences (e.g. parental intake and home availability) using different data sources. We also measured potential confounders of the association between intervention and FV intake (determinants of FV intake which the intervention was not tailored to) such as school nutritional policies, family meal habits, family structure, and ethnic background (not shown in Table 4). Parental SEP (moderator in Figure 1) will be based on questions to parents and pupils on each parent's educational and occupational background.

*Predefined explorative secondary outcomes: changes in positive and negative intended and unintended side-effects*: Intended positive side effects and unintended adverse effects will be measured by questionnaires to the pupils and parents. We will assess whether there are significant changes in these among pupils at intervention schools versus baseline and control group.

Intended positive side-effects: At follow-up, the increased access to FV at intervention schools was expected to significantly decrease proportions of pupils at intervention schools who felt out of energy, had difficulties in concentrating during class in school and who ate unhealthy food almost daily. Also, we expected significant positive changes in pupils' well-being. By use of questionnaires to the school principals, we will measure whether participation in the Boost project has initiated some environmental changes and capacity building at the intervention schools at 2^nd ^follow-up (e.g. initiation of FV programmes, increased sale of FV in schools, increased focus on school food policies or limiting pupils' access to unhealthy food at school).

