#### Response rates and characteristics of pupils at baseline

As shown in Figure 2, response rates were high (> 94%) among both pupils and school principals at intervention-and control schools. A few pupil questionnaires were excluded from the baseline data file because of lack of parental consent. Only three pupil questionnaires were unserious and therefore excluded. The parental response rate was lower in both groups, but higher at intervention schools. Most of the returned parent questionnaires (60%) were completed by female caretakers. The response rates among coaches and managers of sports and youth-clubs were good (> 60%).

Baseline characteristics of pupils from intervention-and control schools were compared by chi-square tests for proportions and *t*-tests for continuous variables to verify the adequacy of the randomisation procedure. The baseline data file included 1,121 pupils from intervention schools and 1,035 pupils from control schools. There were no significant socio-demographic and outcome differences between intervention-and control groups at baseline except for a significant larger percentage of pupils at control schools reporting their parents to be born in Denmark (Table 5). Forty percent of the pupils reached the WHO recommendations of daily FV intake and one fifth accomplished the national recommendations. Less than half of the pupils consumed fruit daily and only one fifth of the pupils consumed raw vegetables daily. The proportions of pupils having access to FV at home, in school and leisure time were almost similar in the two samples at baseline (Table 6). One fifth of the pupils did not attend a sports-or youth club.

**Table 5 T5:** Baseline characteristics of pupils at intervention-and control schools: socio-demographics and primary outcome measures (significant differences are highlighted in bold, p < 0.05)

	Intervention sample (N = 1,121)		Control sample (N = 1,035)		
**Sociodemographics**	**Percentage (N) of pupils reporting the given characteristic**	**N Missing**	**Percentage (N) of pupils reporting the given characteristic**	**N Missing**	**P-value from chi-square test or *t*-test**

Boys	51.8% (581)	0	51.9% (537)	0	p = 0.980

Mother is unemployed*	12.0% (134)	6	10.5% (108)	1	p = 0.169

Father is unemployed*	6.8% (73)	6	5.3% (53)	1	p = 0.237

Mothers' SEP*	26.7% (295)	6	27.9% (286)	2	p = 0.198
High (I + II)	26.7% (295)		29.9% (307)		
Medium (III + IV)	23.9% (264)		21.8% (223)		
Low (V + 7)	22.7% (251)		20.4% (209)		

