**Availability of FV at leisure time activities**					

Always having access to F in at least one sports- or youth club*	25.6% (232)	8	30.0% (245)	9	p = 0.047

Always having access to V in at least one sports- or youth club*	13.0% (118)	8	12.0% (98)	9	p = 0.503

**Abbreviations: **F = fruit, FV = fruit and vegetables, V = vegetables. *415 pupils who did not attend sports-or youth clubs were excluded from the analyses (Intervention sample: N = 207, control sample: N = 208)

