The novelty of the Boost intervention is that it is one of the first large-scale, school-based, multi-component, multi-level interventions to be implemented for a whole school-year and evaluated with long follow-up and in a randomised controlled design in Denmark. It is based on comprehensive reviews of both quantitative and qualitative studies of factors which promote teenagers' intake of FV [3,6], it focuses on 13-year-olds, it targets both fruit and vegetable consumption, it has a strong focus on availability in all settings relevant to teenagers, it implements a free FV programme in a Danish context in combination with educational components, it focuses on changing norms/school class environment/social practise around eating FV, and it explores ways to include sport-and youth clubs in health promotion. The survey instruments measure groups with low intake of FV such as boys and low social class, leaving opportunity for analysis of effect modification. The project tests innovative constructs such as perceived appropriateness of eating FV in different occasions, settings and situations and a multidimensional measure of availability at home and in schools [6]. The thorough process evaluation based on multiple methods and data sources will give a comprehensive picture of characteristics of the intervention and the school (context and composition) influencing implementation of educational and environmental strategies in families, schools and sports-and youth clubs. The study design enables us to examine which methods are efficient in changing specific determinants as we may link changes in determinants to whether the specific components were effectively administered. Successful recruitment of schools and high response rates among pupils have resulted in the desirable number of schools and pupils as estimated in the power calculations. We have succeeded in establishing randomisation. Analysis of baseline data showed almost equivalent groups when considering socio-demographic characteristics, primary outcomes, and FV availability at school, home and in sports-and youth clubs, a good starting point for estimating effects of the intervention at 1^st ^and 2^nd ^follow-up. In spite of the random allocation of schools to intervention-and control groups, significantly larger proportions of pupils at control schools had parents born in Denmark which must be taken into account in the effect analyses.

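### The abstract claims baseline equivalence for club availability without naming the exception in Table 6: fruit access at clubs was 25.6% in the intervention arm and 30.0% in the control arm (printed p = 0.047)

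*Protocol article*

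**What the plan says.** The Discussion part of the abstract states: "There was baseline equivalence between intervention-and control groups for sociodemographics, primary outcomes, and availability at home, school and sports-and youth clubs". The next sentence reports one difference, the larger share of control pupils whose parents were born in Denmark.

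Table 6 lists two club items. For "Always having access to F in at least one sports- or youth club" it prints 25.6% (232) in the intervention sample and 30.0% (245) in the control sample, p = 0.047. For "Always having access to V in at least one sports- or youth club" it prints 13.0% (118) and 12.0% (98), p = 0.503.

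The section on response rates and baseline characteristics says that the arms were "compared by chi-square tests for proportions and *t*-tests for continuous variables". The caption of Table 5 sets p < 0.05 as the mark for a significant difference. The same section describes availability, leisure time included, as nearly similar, and the main Discussion calls the groups nearly equivalent. Both use the qualifier almost, which the abstract omits. The main Discussion then singles out one variable: "significantly larger proportions of pupils at control schools had parents born in Denmark which must be taken into account in the effect analyses".

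The section on proximal outcomes words the goal for the determinants as follows: "significant, positive changes in specific determinants of teenagers' FV consumption at intervention schools at 1^st ^follow-up versus baseline and control schools".

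**The concern.** The abstract draws a conclusion that the article's own table does not support. Fathers' country of birth (84.1% versus 88.3%, printed p = 0.006) was reported as an imbalance and marked for account in the effect analyses. The gap in club fruit access is of the same size, is also printed below 0.05 and comes from the same kind of pupil-level test. Yet no text mentions it.

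The item also matters for interpretation. Availability at clubs is what the club fact sheets aim to change. According to Table 4, managers and coaches were surveyed at intervention schools only, so pupil and parent reports are the only two-arm data on leisure-time availability. Determinants are framed as change versus baseline and control. If that framing were carried out as an unadjusted change comparison, the arm that starts lower would be expected to gain more through regression to the mean. A reader who relies on the abstract would not know to look for this.

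**Working it through.** **Inputs.** Arm sizes: "The baseline data file included 1,121 pupils from intervention schools and 1,035 pupils from control schools". Pupils outside any club, excluded from the club rows (Table 6 footnote): "Intervention sample: N = 207, control sample: N = 208". Missing: 8 and 9. Pupils with access to fruit: 232 and 245 (Table 6).

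**1. Reproduce the printed row.**
- Denominators: 1121 - 207 - 8 = 906 and 1035 - 208 - 9 = 818.
- Proportions: 232/906 = 25.61% and 245/818 = 29.95%, which match the printed percentages.
- Difference: -4.34 points.
- Pearson chi-square = 4.05, p = 0.044. Fisher's exact test gives 0.046 and the continuity-corrected test 0.050. If the missing pupils stay in the denominators (914 and 827), Pearson p = 0.0475, next to the printed 0.047.

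**2. The other Table 6 rows.** Club vegetables: 118/906 - 98/818 = +1.04 points, p = 0.51, in the opposite direction. The four school and home rows reproduce at p = 0.106, 0.816, 0.109 and 0.365.

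**3. Allow for clustering.** Mean attenders per school: m = (906 + 818)/40 = 43.1. Design effect = 1 + (m - 1) x ICC. The Power calculations section gives an ICC of 0.01 for intake. None is given for club access, so the values below are assumptions.

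| ICC (assumed) | Design effect | p |
|---|---|---|
| 0 | 1.00 | 0.044 |
| 0.001 | 1.04 | 0.049 |
| 0.005 | 1.21 | 0.067 |
| 0.01 | 1.42 | 0.091 |
| 0.02 | 1.84 | 0.14 |
| 0.05 | 3.11 | 0.25 |

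The p-value passes 0.05 once the ICC exceeds about 0.0013. The 95% interval for the difference is -8.6 to -0.1 points without clustering and -9.4 to +0.7 points at ICC 0.01.

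**4. Multiplicity.** With six independent tests at 0.05, the chance of at least one p < 0.05 is 1 - 0.95^6 = 26%.

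**5. Consequence for a change comparison, given this gap.** Let the slope be that of follow-up access on baseline access. The documents give no value.
- Unadjusted change from baseline: tilt = 4.34 x (1 - slope). At slope 0.6 this is +1.7 points and at 0.3 it is +3.0 points, towards the intervention. At 0.7 and 0.2 it is +1.3 and +3.5 points.
- Follow-up values with no use of baseline: tilt = -4.34 x slope. This is -1.3 points at 0.3 and -2.6 points at 0.6, against the intervention.
- With the pupil's baseline value as a covariate, the slope is estimated from the data instead of being fixed at 1 or 0.

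**The case against.** A reader might infer that the club component as a whole starts out biased in its own favour, or that the plan has fixed a biased estimator. The documents support neither reading.

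- **Only one of the two club items leans that way.** Club vegetable access is slightly higher in the intervention arm.
- **The gap may well be chance.** The printed p-value ignores school randomisation, p is about 0.09 at an ICC of 0.01, and one borderline result in six tests is unremarkable. Over all possible allocations a change score is unbiased. The tilt exists only conditional on the gap that was observed.
- **No unadjusted analysis of determinants is stated.** The sentence on change versus baseline and control describes a design goal. The planned model is a multilevel regression, which leaves room for a baseline covariate, and the net-effect formula is labelled descriptive and written for intake. How baseline enters the model for secondary outcomes is ordinary analysis-plan detail.
- **The body text is more careful than the abstract**, and the limitations section concedes that the leisure-time component lacks a control group. Table 6 prints the figures openly, and its caption does not repeat the p < 0.05 marking rule of Table 5.

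All of this stands, and it limits the consequence. It does not rescue the abstract. The same pupil-level tests were good enough to report birthplace as an exception, and a non-significant adjusted test would not establish equivalence. Nor does the conditional tilt depend on the p-value.

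**Conclusion.** The point holds in a narrow form. The abstract's unqualified equivalence for clubs conflicts with Table 6, where fruit access is 4.3 points lower in the intervention arm and is printed as significant by the article's own mark. The imbalance is compatible with chance and concerns club fruit only. Neither the primary outcomes nor the other Table 6 items differ significantly.

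The analytical consequence is conditional and of unknown size. An unadjusted change comparison of club fruit access would tilt by about +1.7 to +3.0 points towards the intervention if the slope lies between 0.3 and 0.6, a range that is assumed. Baseline adjustment is therefore a free improvement on the change-from-baseline framing and does not repair a demonstrated error. The severity is low.

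**What to change.** 1. In the abstract, name club fruit access as an exception to baseline equivalence: 30.0% of control pupils versus 25.6% of intervention pupils who attend clubs.
2. In the main Discussion, keep the qualified wording and add the same exception beside parental birthplace.
3. Analyse pupil-reported leisure-time availability, for fruit and for vegetables, at each follow-up in the multilevel model. Use the pupil's own baseline value as a covariate, with a separate category for pupils who attended no club at baseline (207 and 208), instead of an unadjusted change from baseline.

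The cost is two wording changes and one covariate that is already in the baseline file. No further data collection is needed.

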**Trial registration:**

Current Controlled Trials ISRCTN11666034.

## Background

Many adolescents in western countries, including Denmark, do not meet the World Health Organisation's (WHO) recommendations of a daily intake of at least 400 grams of fruit and vegetables (FV) [1,2]. Especially the vegetable intake lags behind [1,2]. Moreover, FV intake among children decreases as they enter the teen years [3]. The international Health Behaviour in School-Aged Children (HBSC) surveys among 11-, 13-and 15-year-olds show a significant decline in proportions of children eating FV daily by age in almost all countries and most consistently among boys [4,5]. The reason for the decline from age 11 to 15 is unknown. Well-established modifiable determinants among children and adolescents are home availability, parental intake and children's FV taste preferences [3] but these factors may not be sufficient to explain age differences in FV intake. Qualitative studies suggest that peers, short term outcome expectancies, situational norms and different aspects of availability such as variety, convenience and attractiveness of FV and access to unhealthy food may be important for teenagers' FV intake [6]. Furthermore, the transition to secondary school may involve new habits and influences for adolescents as they sometimes change school environments, and may exercise more autonomy over their own food choice. They have increased opportunities for eating unhealthily as they are often allowed to leave school during breaks, spend more time and meals together with their friends and have their own money to spend which limits their parents' influence as role models and caretaker for their dietary behaviour. Teenagers' food choice may function as a statement of independence and detachment from parents as well as a symbolic marker of social identity and belongingness to certain peer groups [6-9]. FV intake in the early teens may be crucial as longitudinal studies show that the frequency of FV intake at the age of 13-14 years is a good indicator of frequency of consumption in young adulthood [10,11].

Few interventions have targeted secondary school-aged children (13-18 years of age) and with mixed results [12,13]. Reviews of intervention studies among children and adolescents have concluded that theory-based, multi-component school-based approaches of a long duration and intensity combining educational and environmental strategies in school with parent involvement are most effective in increasing FV consumption [12,14,15].

### Availability of FV

The importance of availability of FV for adolescents' FV intake has been confirmed in literature reviews of both qualitative studies, observational studies and intervention studies [3,6,12,14,15]. Intervention studies in Norway, Belgium, and Canada have shown that free provision of fruit and/or vegetables in schools can increase adolescents' fruit and/or vegetable intake [16-21]. Studies from Norway suggest that free FV programmes are more effective than subscription programmes in increasing fruit consumption [18]. Subscription programmes may increase social inequality in FV intake as subscribers include mainly high income families whereas free provision increases intake among adolescents from families of low socioeconomic position (SEP) as well [18]. Most interventions have reported larger effects for fruit intake than vegetable intake [21-24] and it remains a challenge to develop effective methods to increase vegetable consumption.

Many intervention studies have only succeeded in increasing FV intake in school, not the total daily intake which may be explained by minimal parental involvement and by the fact that FV provided in schools replace some of the FV eaten at other times of the day [19,22]. Implementation of home components is challenging as few parents tend to participate [25,26]. Home availability and accessibility, parental intake, and SEP are all consistently associated with adolescents' FV consumption [3,27]. It is therefore important to develop strategies which increase parental involvement and support to adolescents' FV intake [28]. The Pro Children multi-component intervention programme which included a family component (parental newsletters, family home assignments) together with FV provision (free or subscription) and a classroom curriculum had a significantly positive effect on total daily fruit-, vegetable-and FV intake among 10-11-year-olds in Norway, the Netherlands and Spain at 8-month follow-up [21].

Multi-component interventions have been suggested to be more effective than single component strategies due to synergistic effects between educational and environmental strategies [29]. Other studies suggest that a single strategy which only increases access to FV is equally or even more effective in increasing adolescents' FV intake [17,30]. Intervention components such as curricular activities are not always implemented as intended. Low fidelity and small doses delivered challenge the validity of assessments of the effectiveness of multi-component interventions [31-33]. Therefore, thorough process evaluation, including detailed monitoring of the implementation is important [32,33].

Computerised individualised tailoring of nutrition education seems to be an effective method of nutrition interventions among adults [34,35]. The evidence for the effectiveness among adolescents is unclear [36-38]. The method has the potential to be an effective intervention strategy as it is a popular intervention activity in this age group [39]. A review from 2010 concluded that dynamically tailored interventions (ipsative feedback) had increased efficacy over time as compared with tailored interventions based on one assessment only [40]. However, this approach has not been widely tested among adolescents.

Many intervention studies suffer from methodological limitations such as lack of randomisation, lack of baseline measurements, low response rates, inadequate adjustment for clustering of schools, short duration of intervention, short follow-up period, lack of explicit theoretical basis, lack of an explicit programme theory (causal model), and lack of process evaluation [13,36,38,41]. Furthermore, evaluation studies of multi-component interventions often report the collective, synergistic effect of the intervention as it is challenging to disentangle the relative importance of specific components. Evaluation of different combinations of strategies using multi-arm controlled designs requires substantial statistical power [19,20] and there is a need for new approaches to decompose the effects.

Many FV intervention studies have used determinants as proximal outcomes and measured changes in these. Fewer studies have examined if changes in FV intake were preceded by changes in determinants (mediation analyses) and even fewer have linked changes in determinants to implementation of specific intervention components. In order to make valid interpretations of the proximal outcomes (determinants) of the intervention and examine which methods are efficient in changing each of these determinants we need to know whether the specific components were effectively administered [32,42]. Moreover, there is a lack of insight in programme reach and differential effects on proximal (determinants) and distal outcomes (FV intake) in population subgroups with low intake such as boys and low income groups. Few studies have examined how and if these subgroups benefit from interventions [43] and if intervention components reach all subgroups equally (effect modification analyses).

It is important to promote access to FV in the multiple settings of adolescents' lives to consistently support them in making healthy food choices throughout the day. Despite this fact most nutrition interventions have addressed the school-or home environment and not the neighbourhood and leisure time activities. There is a great potential in sports-and youth clubs to promote healthy eating habits to adolescents in their leisure time [44]. Cross-sectional studies from Australia, Finland and Denmark have pointed at factors promoting unhealthy eating habits in sports clubs [44-47]. The same challenges are found in youth clubs in Denmark [48]. A Cochrane review from 2008 concluded that there is a lack of controlled studies evaluating policy interventions aiming at enhancing health behaviours through sporting organisations [49].

Given the rationale above, the aim of the Boost study was to develop, implement and evaluate a comprehensive school-based and community-integrated intervention which produces a persistent increase in FV consumption among teenagers. The key component of the intervention programme was to improve the determinants for FV intake, especially to enhance availability of FV in the multiple settings in which teenagers take part. The developmental work was to be guided by theory, evidence and best practise. This paper presents the development of the intervention, the design of the effectiveness study, and the baseline characteristics of pupils at intervention-and control schools.

